## Abstract

**Background:**

Patients with delirium and dementia admitted to general hospitals have poor outcomes, and their carers report poor experiences. We developed an acute geriatric medical ward into a specialist Medical and Mental Health Unit over an eighteen month period. Additional specialist mental health staff were employed, other staff were trained in the 'person-centred' dementia care approach, a programme of meaningful activity was devised, the environment adapted to the needs of people with cognitive impairment, and attention given to communication with family carers. We hypothesise that patients managed on this ward will have better outcomes than those receiving standard care, and that such care will be cost-effective.

**Methods/design:**

We will perform a controlled clinical trial comparing in-patient management on a specialist Medical and Mental Health Unit with standard care. Study participants are patients over the age of 65, admitted as an emergency to a single general hospital, and identified on the Acute Medical Admissions Unit as being 'confused'. Sample size is 300 per group. The evaluation design has been adapted to accommodate pressures on bed management and patient flows. If beds are available on the specialist Unit, the clinical service allocates patients at random between the Unit and standard care on general or geriatric medical wards. Once admitted, randomised patients and their carers are invited to take part in a follow up study, and baseline data are collected. Quality of care and patient experience are assessed in a non-participant observer study. Outcomes are ascertained at a follow up home visit 90 days after randomisation, by a researcher blind to allocation. The primary outcome is days spent at home (for those admitted from home), or days spent in the same care home (if admitted from a care home). Secondary outcomes include mortality, institutionalisation, resource use, and scaled outcome measures, including quality of life, cognitive function, disability, behavioural and psychological symptoms, carer strain and carer satisfaction with hospital care. Analyses will comprise comparisons of process, outcomes and costs between the specialist unit and standard care treatment groups.

**Trial Registration number:**

ClinicalTrials.gov: NCT01136148

## Background

Two-thirds of UK National Health Service (NHS) general hospital (i.e. non-psychiatric) beds are occupied by people over 65. Previous reports suggest that 60% of this age group have, or develop, a mental health problem, including dementia (about 30%), delirium (about 20%) and depression (about 30%). About 10% of elderly medical in-patients have significant behavioural disturbance [1].

Ill older people with mental health problems fit uneasily into general hospital services. Presentations can be non-specific (falls, immobility, worsening confusion, not coping). Patients are prone to deterioration and complications. Many general hospital staff feel ill-equipped to assess or manage them. Outcomes are worse (high rates of mortality and care home placement), and length of hospital stay is longer than for people without mental health problems [1]. Relatives are often stressed and dissatified with care [2].

Nationally in the UK, there are some specialist psychiatric liaison services for older people, and a few joint medical-psychiatric units. Such services have been advocated recently in policy documents [1,3,4], but little research has been done on the particular needs and problems of this group, or the best way to configure services to address them. The National Dementia Strategy calls for improvements in care for people with dementia admitted to hosptial, but without providing details on how to do this [5].

There is good evidence that co-ordinated, systematic, multidisciplinary care for people with stroke improves outcomes [6]. The approach called 'comprehensive geriatric assessment', including diagnostic, functional, psychological, social and environmental dimensions, improves outcomes for older people with complex health problems [7].

We hypothesised that a specialist unit for people admitted as emergencies to a general hospital with concurrent dementia or delirium would be similarly effective, and cost-effective. We developed a specialist Medical and Mental Health Unit (MMHU) over a period of eighteen months [8], before undertaking an evaluation by controlled clinical trial.

The trial forms part of a National Institute for Health Research programme, Medical Crises in Older People [9]. The first phase comprised recruiting and following up a cohort (or case series) of 250 older people with mental health problems admitted as an emergency to a general hospital. The recruitment procedures and documentation for this study were almost identical to those intended for the trial, representing a pilot study of the methods.

## Methods/design

### Main research hypothesis

Patients admitted as an emergency to a general hospital with concurrent 'confusion' and managed on a specialist ward (MMHU), will spend more days at home out of the 90 days following randomisation, than those receiving standard care [10].

### Secondary hypotheses

Compared with standard care, management on the MMHU will be associated with:

1. lower mortality

2. better quality of life, less behavioural disturbance, and less disability after 90 days

3. fewer readmissions, reduced total hospital stay over 90 days, and fewer new care home placements

4. greater satisfaction with hospital care amongst family carers

5. less carer strain and psychological dysfunction.

Management on the MMHU is cost-effective compared with standard care.

Management on the MMHU is associated with better quality of care and patient experience in a concurrent observational study.

### Overview of study design

Potentially suitable patients are referred to MMHU by clinical staff on the Acute Medical Admissions Units, within 24 hours of admission. MMHU staff record details on a computerised screening log. An algorithm allocates patients either to MMHU or a standard care ward, some at random, others not (Figure 1). If allocated to MMHU the patient is transferred immediately. If allocated standard care, an alternative bed is found by Admissions Unit staff.

**Figure 1 F1:**
[figure not shown]
**Randomisation and bed management algorithm**. Patients with codes <4000 are randomised with stratification according to care home residence or not, and are approached for trial inclusion. Patients with codes >4000 are not randomly allocated, and are not eligible for trial inclusion.

Research staff monitor the list of randomly allocated patients, and, as soon as they can be contacted, invite them, and a carer, to take part in the trial. If they agree, baseline data are collected. Satisfaction with care is recorded by the carer one to three weeks after discharge; other outcomes are ascertained by interview 90 days after randomisation. Quality of care and patient experience are assessed by observation. Resource use is collected by questionnaire, and from electronic service records.

The trial flow diagram is given in Figure 2.

**Figure 2 F2:**
[figure not shown]
**Trial flow diagram**.

### Inclusion criteria

The study population comprises patients admitted to the Acute Medical Admissions Unit of a single large teaching hospital (providing sole emergency general medical services for its catchment population), who are aged over 65, and thought to be 'confused' on initial assessment by the clinical team responsible for their care. 'Confusion' is not defined further. This definition is broad and simple enough to allow identification and referral of suitable patients by non-specialist Admissions Unit staff, without causing delay in the admission pathway. In practice, almost all patients identified as 'confused' have delirium and/or dementia.

We also try to recruit a family member or carer participant, where one is available and willing, to act both as an informant, and in order to study impact on carer health. A carer is defined as a non-professional, who sees the patient at least once a week, most weeks, for at least one hour.

### Exclusion criteria

• Patients fulfilling clinical exclusion criteria:

○ severely medically ill, requiring intensive monitoring or therapy (critical care), or specialist medical intervention (e.g. severe acute gastrointestinal bleeding, respiratory support)

○ those with an overriding clinical need for another service, such as orthopaedics, or acute stroke

○ acute intoxication or overdose

○ those detained under the Mental Health Act.

• Patients admitted to the MMHU or standard care, who have not been randomised.

• Patients resident outside of Nottingham City or Nottinghamshire County Primary Care Trust (PCT) areas, for whom data on health and social care resource use could not be ascertained using routine electronic sources. (PCTs are service commissioners in the English NHS).

• Patients and carers unable to speak English, with no available family or other non-professional translator.

### Randomisation

#### Screening log

All referrals are entered on to an internet-based computerised screening log, hosted by the Nottingham University Clinical Trials Unit.

#### Bed management

We developed an algorithm to manage beds and randomly allocate patients (Figure 1). This was refined over several months of piloting. The precise details reflect local geography, service demands and patient admission rates, taking account of day-to-day variation in both bed availability, and presentation of suitable new patients:

• Randomisation can only take place if there is a bed available on the MMHU (if not, the patient is non-randomly allocated standard care, and is not eligible for trial inclusion)

• The last two beds on the MMHU are always available for randomisation, with the exception of patients referred between midnight and 7 am (a few patients only, to minimise difficult negotiations with bed managers overnight; these are not eligible for trial inclusion)

• If there are four or more beds available on the MMHU, patients are admitted without randomisation (and are not eligible for trial inclusion).

• Patients are also admitted to the MMHU without randomisation (and are not eligible for trial inclusion), if there are three or more empty beds, and patients are:

○ referred from psychiatric wards, following assessment for suitability

○ referred from other hospital wards, following assessment for suitability, but only if not previously randomised to standard care

○ resident outside the Nottingham PCTs areas.

#### Sequence generation

The randomisation sequence is generated using a computer random number generator, in a 1:1 ratio, and a permuted block design with varying block sizes up to 6, stratified by prior care home residence.

#### Allocation concealment

The randomisation sequence is concealed from clinical staff who use the computer to allocate patients. However, research staff collecting baseline data are not blind to treatment allocation.

#### Implementation

A research nurse actively liaises with bed managers during the working day. Out-of-hours a senior clinician (consultant) investigator is always on-call to deal with bed management problems. In practice, the algorithm randomises sufficient patients to recruit our target of between eight and 10 participants per week, whilst remaining acceptable to hospital managers. Readmitted patients are accommodated according to their original allocation.

### Treatment definition: Intervention and control groups

The two arms of the trial are:

• Intervention arm: allocation to MMHU

• Control arm: allocation to standard care ward.

Treatment comprises the 'package' of care delivered on the MMHU or standard care wards [8]. These represent complex ('black box') interventions, akin to that provided on stroke units for stroke patients. There is evidence that the overall effect of such units is greater than the sum of identifiable parts [11,12].

The pathway of hospital care for all patients includes admission to an Acute Medical Admissions Unit following referral from a general practitioner, or via the hospital Emergency Department. Following assessment by a senior physician (not necessarily specialising in the care of older people), patients are allocated to a ward.

All wards have access to doctors, ward-based and specialist nurses, physiotherapy, occupational therapy, speech and language therapy, and dietetics. Complex discharge planning and assessment for rehabilitation is supported by a separate multidisciplinary advice team. Mental health support is provided on a consultation basis by psychiatrists from a separate NHS organisation (Mental Health Trust). Social care assessments (provided by local government authorities, not the NHS) are available on request, regardless of ward allocation. All patients, in both settings, are eligible for consideration for standard mental health services, rehabilitation, intermediate and social care.

#### Standard care

'Standard care' wards include four acute geriatric medical wards, and six general medical wards (with acute medicine, respiratory, diabetes, gastroenterology or rheumatology as their specialist interests). As a matter of policy, the hospital tries to avoid placing confused older medical patients on surgical wards or transferring them (as 'sleepers out') after admission, if there are insufficient medical beds.

Practice on acute geriatric medical wards is based on multidisciplinary comprehensive geriatric assessment, and many staff have considerable experience, and varying degrees of expertise, in the management of delirium and dementia. These wards provide most of the 'standard care' for confused older people.

#### Medical and Mental Health Unit

The MMHU was developed over 18 months prior to trial commencement. The unit was previously a 28-bedded acute geriatric medical ward. We have described the development and philosophy of the ward elsewhere [8]. In brief, we enhanced five componants:

• Specialist mental health staff additional to the normal ward complement of medical, nursing and therapy staff, comprising three registered mental health nurses, a specialist mental health occupational therapist (OT), 0.5 whole time equivalent (WTE) specialist physiotherapist, 0.2 WTE speech and langauge therapist, 0.2 WTE additional geriatrician time and 0.1 WTE psychiatrist time, and four unregistered health care assistants, two of whom took on the role of activities co-ordinators. New documentation was introduced for mental health assessments and OT interventions.

• Training for all staff in the philosophy of person-centred dementia care. This emphasises respect for the person with dementia as an individual with a history, values and preferences, and the right to make choices. Confrontation is avoided, and activity and diversion promoted, based on making meaningful connections with the person with dementia's retained abilities.

• A programme of therapeutic and leisure activites was instituted to try to maintain abilities, prevent distress behaviours, and promote night-time rest. Patients are got up and dressed if not too ill.

• The environment was made more appropriate. The ward had to relocate after nine months of development, to one which was longer and with better lay out, when it was realised that sufficient adjustments could not be made in the original one. Noise (such as from radios and equipment alarms) is minimised. Orientation cues, appropriate signage and some safety modifications were made. Bed spaces are personalised.

• A proactive and inclusive approach to family carergivers is promoted, with active communcation, involvement in decision making, and inclusion in hands on care, if willing.

#### Contamination

The hospital Trust is developing a strategy of improvement in dementia care, to which members of the MMHU staff have contributed. Other hospital staff are aware of the MMHU, and may have attended teaching or presentations on its work. Some therapy and medical staff work across wards, in particular out-of-hours, or to cover shortages elsewhere, but the additional specialist staff do not. Many hospital-wide policies, such as on nutrition, mental capacity, infection control, end of life care, continence, falls prevention and medicines management are of great relevance to patients with delirium and dementia, and these are promoted on an ongoing basis.

The study therefore represents an evaluation of the additional benefit of care in a geographically-defined unit, with additional staffing and training, and following best practice, beyond that achievable in standard hospital care.

### Recruitment and consent

As soon as possible following ward allocation, research staff identify patients who have been randomised. After introduction to the researcher, the patient is assessed for mental capacity to give or withhold consent for participation in the trial. This means understanding, retention, reasoning and communication ability sufficient to decide on willingness to undergo baseline and follow up data collection, and recording use of health and social care. This assessment is done by discussion, using a printed information sheet, supplemented by a simple and short summary, and a checklist of requirements set out in the Mental Capacity Act 2005 [13].

Those having capacity are invited to give written consent to participation. We also ask permission to approach a family member or carer. The family member or carer is given an information sheet and asked to give consent for his or her own involvement in the study.

Most potential participants lack capacity. The procedures set out in section 32 of the Mental Capacity Act are then followed. A family member or carer is asked to act as a 'personal consultee', and asked if they have any reason to believe the patient would not have wanted to take part. If willing, they sign a consultee agreement form. Carers are asked for their own consent to participate.

If there is no contactable carer, or if the carer lacks capacity, the nurse in charge of the ward is asked to act as a 'professional consultee' under section 32(5) of the Mental Capacity Act. If he or she knows no reason why the patient would not want to participate, the patient is included. Most patients in this situation are resident in care homes, and background data are collected from care home staff.

### Patients not recruited into the study

Patients not recruited into the study continue with care on the MMHU, or standard care ward, and have no contact with research staff. In practice, ward staff are not aware of who is or is not in the study, even though this is recorded in the case notes, and no distinction is made between recruited and non-recruited patients in care given.

### Baseline measurements

Data collection is by interview with a trained researcher. These are either registered nurses or psychology graduates. Information is collected from the patient participant if possible, corroborated by a carer, or taken from family members or carers as informants. Carers are invited to complete a self-report questionnaire, or are interviewed to complete the same information, if they prefer. Medical and nursing notes are scrutinised for diagnostic, drug and functional information.

Baseline data include:

• Social and demographic information, including co-residence and type of accommodation

• Cognitive impairment (Mini-Mental State Examination [14])

• Delirium diagnosis and severity (Delirium Rating Scale [15])

• Quality of Life (Euroqol EQ5D [16])

• Prior and current physical disability (Barthel index [17])

• Behavioural and psychological symptoms (Neuropsychiatric Inventory [18])

• Medical diagnoses

• Drugs taken on admission

• Illness severity (Modified Early Warning Score [19])

• Hospital admission in the previous year

• Carer relationship, co-residence and amount of care given

• Carer strain index [20]

• Carer psychological distress (GHQ-12 [21]).

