Multiple linear, logistic, Poisson and Cox regression will be used, as appropriate to the error distribution of each outcome variable, to model the difference between treatments, adjusting as appropriate for apparent baseline differences, and for other prognostically important variables to improve the precision of effect estimates. We will explore the fit of alternative statistical models for days at home, which will take account of the non-standard distribution of this variable constrained to take values between zero and 90 days, and with an excess of zero values. Non-parametric continuous data will be transformed to normality where possible or otherwise analysed using Mann Whitney U-test. The intervention effect parameter will be presented as an estimate with 95% confidence intervals.

We will use imputation methods for dealing with missing values from those who withdraw, die, or otherwise do not provide follow-up data. We will conduct sensitivity analyses to explore the robustness of the results to alternative assumptions about the randomness of missing data.

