### Additional measures to avoid bias

Studying people in urgent care settings unavoidably carries risk of bias. We introduced explicit steps to try to minimise that risk.

Researchers are aware of potential problems with bias, and are trained to adopt a rigorous approach to recruitment, whilst respecting an individual's right not to be involved in research if they so choose, or if circumstances (such as end of life care) make it inappropriate.

Research staff operate shifts to be available when family carers are visiting, to maximise recruitment. A contact log is maintained. The proportion of randomised patients recruited in each setting is monitored closely.

Extensive data is collected at baseline from recruited participants that will enable comparison of groups, and statistical adjustment for baseline imbalances if found.

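### Baseline covariates taken from ward notes after allocation could be recorded differently by arm, and adjusting for them could bias the days-at-home estimate

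*Protocol article*

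**What the plan says.** The relevant statements are spread over several sections of the protocol article.

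- **Timing** (Recruitment and consent): "As soon as possible following ward allocation, research staff identify patients who have been randomised". Baseline data follow recruitment, so they are gathered when the patient is already on the allocated ward.
- **Blinding** (Allocation concealment): "research staff collecting baseline data are not blind to treatment allocation".
- **Sources** (Baseline measurements): the main route is interview, "Data collection is by interview with a trained researcher", and there is a second route, "Medical and nursing notes are scrutinised for diagnostic, drug and functional information". Table 1 lists a medical data form completed from case notes. Medical diagnoses are a listed baseline item with no named instrument. Cognition, delirium, function and behaviour each have a named scale.
- **Record keeping on the MMHU** (Medical and Mental Health Unit): "New documentation was introduced for mental health assessments and OT interventions". The unit also gained mental health nurses, a specialist occupational therapist and psychiatrist time. Under Contamination, some therapy and medical staff are said to work across wards, "but the additional specialist staff do not".
- **Use of the baseline data**: the regression models estimate the treatment difference "adjusting as appropriate for apparent baseline differences" (Descriptive statistics, univariate and multivariate analyses). Additional measures to avoid bias relies on "statistical adjustment for baseline imbalances if found" as a safeguard against selective recruitment.

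**The concern.** A covariate used to adjust a treatment effect should not depend on the treatment. Here part of the baseline record comes from notes that may have been written on the allocated ward, and what is written there may depend on who assesses patients and on which forms. If the MMHU notes a diagnosis more completely, two groups of equal severity would look unequal. The protocol tests baseline differences for significance because recruitment follows randomisation, so such an artefact could be taken for recruitment bias and then adjusted away. The adjusted analysis would credit the arm with fuller notes with sicker patients than it has, and so with better results than it achieved.

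Adjustment carries unusual weight in this design because it is the stated answer to post-randomisation recruitment. The sections on implications of the design and on avoiding bias discuss who is recruited. They do not consider whether the baseline record itself depends on the ward.

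**Working it through.** The protocol gives no figure for recording rates, so there is no figure of its own to reproduce on this point. The calculation below shows the size the mechanism could have.

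**From the protocol article:** 1:1 allocation, 300 per group, target difference 5 days.

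**Assumed:** no true treatment effect; a binary condition with the same true prevalence *p* in both arms; the condition lowers days at home by *c*; it is recorded in a fraction *s₁* of true cases on the MMHU and *s₀* on standard wards, with no false recording; linear regression of days at home on arm and recorded condition.

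**Formula.** Recorded prevalence is *r₁ = p·s₁* and *r₀ = p·s₀*. The slope on the recorded condition, pooled within arms, is

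b = −c(1 − p)(s₁ + s₀) / [s₁(1 − r₁) + s₀(1 − r₀)]

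and the spurious adjusted effect of the MMHU is −b(r₁ − r₀).

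**Larger gap, p = 0.7, recording 95% v 75%, c = 15**
- r₁ = 0.665, r₀ = 0.525, difference 0.14
- b = −15 × 0.3 × 1.7 / (0.95 × 0.335 + 0.75 × 0.475) = −7.65 / 0.6745 = −11.34
- bias = 11.34 × 0.14 = **+1.59 days**, or 1.59/5 = 32% of the target difference

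**Smaller gap, recording 90% v 80%, c = 15**

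| Prevalence | r₁ v r₀ | b | Bias (days) | Share of 5 days |
|---|---|---|---|---|
| 0.7 | 0.63 v 0.56 | −11.17 | +0.78 | 16% |
| 0.5 | 0.45 v 0.40 | −13.08 | +0.65 | 13% |
| 0.3 | 0.27 v 0.24 | −14.11 | +0.42 | 8% |

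**Checks on direction and limits**
- Equal recording: r₁ − r₀ = 0, so the bias is 0.
- Rates swapped (75% v 95%): −1.59 days. The sign follows whichever arm records more.
- At 50% prevalence, with *c* from 5 to 20 days and recording gaps from 90% v 80% to 100% v 50%, the bias runs from 0.2 to 4.3 days.
- If the model also holds a measured scale that separates true cases by 1 to 2.5 standard deviations and is unaffected by ward, the 1.59 days falls to about 1.5 to 1.1.

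**Would the artefact be noticed as an imbalance?** For 66.5% v 52.5% with 300 per arm, the standard error is √[(0.665 × 0.335 + 0.525 × 0.475)/300] = 0.0397 and z = 0.14/0.0397 = 3.5, so it reaches p < 0.05 in about 94% of trials. For 63% v 56%, z = 0.07/0.0400 = 1.75, about 42%.

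**Effect on false positives.** With an assumed residual SD of 33 days, the standard error of the treatment effect is 33 × √(2/300) = 2.69 days. A bias of 1.59 days is 0.59 standard errors. The two-sided 5% error rate becomes Φ(−1.96 + 0.59) + Φ(−1.96 − 0.59) = 0.085 + 0.005, about 9%.

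**The case against.** The case against has real substance.

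- **Interview is the main route.** Delirium, function, cognition and behaviour have named scales. Demographics, drugs on admission and earlier admissions are little exposed. This stands and narrows the concern to medical diagnoses, and to function where the notes supply it.
- **Therapy notes are not named at baseline.** The baseline section mentions medical and nursing notes. Therapy notes appear only in the 90-day review of care processes. So the text does not show that the specialist occupational therapist's forms reach the baseline data.
- **Standard wards also assess patients.** The geriatric wards, which give most of the standard care, practise comprehensive geriatric assessment, and all wards have therapists and psychiatric consultation. This would shrink any gap. It does not remove the difference in added staff and forms, and six general medical wards are also in the control arm.
- **The abstraction window may be on the data form**, which is not shown, and adjustment is only as appropriate. This is fair. Even so, the article describes a source that post-dates allocation, and an analysis plan cannot impose a cut-off later unless entry dates are captured.
- **An unadjusted comparison is planned.** It is free of this mechanism, but it remains open to the recruitment bias that adjustment is meant to address, so it does not make the adjusted result dispensable.

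A reader might go further and infer that MMHU patients will look sicker and that adjustment will turn a null effect into a benefit. The documents do not support that. They report no recording rates by arm. The direction is an inference from staffing and forms, and early MMHU care or unblinded rating could push the other way.

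**Conclusion.** The concern holds as a risk of bias in the adjusted analysis only. Note-derived baseline covariates are collected after allocation, by unblinded staff, with no stated limit to earlier entries, and the documentation arrangements differ between arms. Adjustment could then shift the days-at-home effect in either direction.

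Under the assumptions shown, a modest recording gap costs under 1 day and the larger one about 1.6 days of the 5-day target. In the larger case the false-positive rate rises to about 9%, so a spurious finding becomes more likely without becoming the expected result. These sizes rest wholly on assumed prevalence, recording rates and cost in days. The point merits a change because the remedy is cheap and is best applied while the notes are being abstracted.

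**What to change.** 1. For covariates and for judging baseline balance, use only case-note entries dated before allocation: the Admissions Unit assessment and earlier records, from the same sources in both arms. Every patient is assessed on the Admissions Unit before being allocated to a ward, so a common source exists.
2. Record the entry date for each note-derived item on the medical data form.
3. Treat diagnoses or functional findings first recorded on the allocated ward as process data. Do not use them as covariates or as evidence of imbalance.
4. Report the unadjusted days-at-home estimate beside the adjusted one.

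The cost is one instruction and a date check on the form. Some diagnostic and functional detail will be lost where the admission clerking is thin.
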